#### (2) Neuro-navigation

The rTMS stimulating sites were identified on the 3D brain reconstruction using a neuro-navigation system (Brainsight, Rogue Research Inc., Montreal, QC, Canada). Before the experiment, T1 weighted images were individually obtained from each patients using rapid acquisition gradient echo sequence (Philips Ingenia 3 Tesla, MPRAGE, TR/TE = 2000ms/4.6 ms, voxel size = 0.98 mm × 0.98 mm × 1.2 mm, the field of view = 250 mm × 250 mm × 240 mm, 200 sagittal slices). To localize the rTMS sites, the method described by Mylius et al. [18] were used. Briefly, the boundary of the middle frontal gyrus (MFG) was firstly drawn on the neuro-navigated 3D brain reconstruction, then the DLPFC target was determined on the middle of the bonder line between the anterior one third and the posterior two thirds of the MFG. Similarly, the IFG target was determined on the middle of the transverse intermediate line of the inferior frontal gyrus (IFG), the TPC target was determined on the middle of the border line between the supramarginal gyrus (SG) and the angular gyrus (AG). All the rTMS stimulating sites were selected on the affected cerebral hemisphere.

#### (3) RMT

The resting motor threshold (RMT) is defined as the lowest stimulation intensity to induce a, at least 50% of the time in a finite number of trials (typically 10 trials).

The RMT was determined as the minimum stimulating intensity necessary to elicit an overt motor response (motor evoked potential, MEP, larger than 50 μV) in the right abductor pollicis brevis (APB) at least 5 of 10 times [19].

#### (4) Route medical cares

The route medical cares based on the individualized illness for each patient are permitted but the medications for improving cognition such as Pfizer’s Aricept were prohibited during the trial.

#### (5) Discontinuing criteria

Patients who simply wishes to stop participation;Patients who could not undergo the baseline assessment;Patients who did not complete the rTMS treatment sessions;Patients who suffered from worsening symptoms.

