#### (3) Participant timeline

Study will commence with the eligibility screen for participants. Once eligibility is confirmed, the patient will sign an informed consent and be allocated to one of nine active rTMS group. Clinical assessments and functional magnetic resonance imaging (fMRI) scan will be performed at baseline (W0), termination of 20 rTMS sessions (W5) and the follow-up (W17). In the any phase of the study procedure, we will record the number and reasons for any participants who will be excluded or any who will decline consent or withdraw from the study. The SPIRIT schedule and the flowchart of the study are presented in Fig 1.

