#### (5) Recruitment

This trial aims to recruit 45 in- or outpatients with PSCI in the West China Hospital of Sichuan University who are recommended by the rehabilitation physicians, therapists, or any other medical practitioners and willing to receive rTMS treatment. Once the oral consent to take part in the study is confirmed, written and verbal information about the study aim and procedures is provided to all the volunteer participants. There are no biological specimens collecting for storage and anticipated harm for the participants throughout the study. All the personal information and any other data about the potential or enrolled patients will be traceable in the medical records and available from the corresponding author on request in order to protect confidentiality. After the written informed consents are obtained from the eligibility-screened participants, the study will commence with the baseline assessment and then the randomized allocation.

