### 3. Outcomes

The primary outcomes are the Montreal Cognitive Assessment Beijing Version (MoCA-BJ) and the Trail-Making Test (TMT). The secondary outcomes are the modified Barthel index (MBI), the Lawton Instrumental Activities of Daily Living Scale (LIADL), the stroke-specific quality of life (SS-QOL), the functional magnetic resonance imaging (fMRI) scan and the adverse events. All measurements of clinical assessments were administered three times: pre-treatment (baseline), post-treatment, and at a three-month follow-up. All of the cognitive assessments were performed by a trained neuropsychologist who was blind to the treatment status of the participants throughout the study. The MRI scan were conducted at baseline and at the end of rTMS treatment.

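### The discontinuing criteria do not separate stopping rTMS from leaving the study, so week 5 and week 17 outcomes may be lost in relation to tolerability and possibly response

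*Protocol article*

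**What the plan says.** Under Methods, 2. Interventions, (5) Discontinuing criteria, the article gives one undivided list of four items. The first two are "Patients who simply wishes to stop participation;Patients who could not undergo the baseline assessment". The last two are "Patients who did not complete the rTMS treatment sessions;Patients who suffered from worsening symptoms". The consequence of meeting a criterion is not stated, and worsening is not defined.

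Four other places bear on how the list is read:

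- 1. Patients, (3) Participant timeline: assessments are "performed at baseline (W0), termination of 20 rTMS sessions (W5) and the follow-up (W17"). For exclusions and withdrawals, the commitment is that "we will record the number and reasons for any participants who will be excluded or any who will decline consent or withdraw from the study".
- 1. Patients, (5) Recruitment: after consent, "the study will commence with the baseline assessment and then the randomized allocation".
- 3. Outcomes: "All measurements of clinical assessments were administered three times: pre-treatment (baseline), post-treatment, and at a three-month follow-up".
- 3. Outcomes also names the primary endpoints: "The primary outcomes are the Montreal Cognitive Assessment Beijing Version (MoCA-BJ) and the Trail-Making Test (TMT").

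**The concern.** Stopping a treatment and leaving a study are different events. A patient who stops rTMS early because of headache, or whose condition declines, can still be tested at the scheduled visits. If the list is applied as study exit, whether a patient has an outcome depends on how well that patient tolerated the assigned settings and perhaps on how well they worked.

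The trial compares nine active combinations in order to choose the best level of each parameter. The arms differ in intensity (90, 100 or 110% of resting motor threshold) and in pulse number (1000, 1500 or 2000), so tolerability could differ by arm. The groups have 5 patients each, so one exit removes 20% of a group. A conduct rule also differs from an analysis choice: a later analysis plan cannot restore assessments that were never made.

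**Working it through.** **1. Reading the text.** The table sets each item against the two readings.

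| Item | As a reason to stop rTMS | As a reason to leave the study |
|---|---|---|
| Patient wishes to leave | Poor fit: a study-level act | Fits |
| No baseline assessment | Poor fit: baseline precedes allocation, so there is no rTMS to stop | Fits |
| rTMS course not completed | Poor fit: rTMS has already stopped | Fits |
| Worsening symptoms | Fits | Fits |

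The timeline section ties the W5 visit to the end of 20 sessions. It promises to record how many leave and why, and says nothing of continued assessment. Study exit is therefore at least as natural a reading as a treatment stop.

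**2. The plan's own figure.** 9 groups × 5 = 3 site levels × 15 = 45, as stated under Sample size. The article gives no SD, effect size, loss rate or definition of worsening. Every input from here on is an assumption, for illustration only.

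**3. Fragility of the groups.** With exit probability d, the chance that a group of 5 loses at least 2 is 1 − (1−d)^5 − 5d(1−d)^4. The chance that at least one of nine groups falls to 3 or fewer is 1 − (1 − that)^9.

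- d = 5%: 1 − 0.7738 − 0.2036 = 0.0226, giving 1 − 0.9774^9 = 19%.
- d = 10%: 1 − 0.5905 − 0.3281 = 0.0815, giving 1 − 0.9185^9 = 53%.

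**4. Loss through worsening that tracks response.** Let X be MoCA change and L the variable that triggers removal. Both are normal with mean μ and the same SD, with correlation ρ; the patient is removed if L ≤ c. Then

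E[X | L > c] = μ + ρ·SD·φ(a)/(1 − Φ(a)), with a = (c − μ)/SD.

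Base case: SD 3, level means 1, 2, 3, 15 per level, ρ = 0.6. For c = −3:

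- μ = 1: a = −1.333, added bias 1.8 × 0.1640/0.9088 = 0.325.
- μ = 3: a = −2, added bias 1.8 × 0.0540/0.9772 = 0.099.
- The true difference of 2.0 becomes 2.0 + 0.099 − 0.325 = 1.775.

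| Threshold c | Lost at μ = 1 / 2 / 3 | Difference, ρ = 0.6 | Difference, ρ = 0.3 |
|---|---|---|---|
| −3 | 9.1% / 4.8% / 2.3% | 1.775 | 1.887 |
| −2 | 15.9% / 9.1% / 4.8% | 1.670 | 1.835 |
| 0 | 36.9% / 25.2% / 15.9% | 1.440 | 1.720 |

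**5. Chance of picking the best level** (400,000 simulations, SD 3, 15 per level). With no loss it is 80.6%. Random loss at the same rates separates the effect of smaller n from that of selection.

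| Threshold c | Random loss | Selective, ρ = 0.6 | Selection cost, ρ = 0.6 (points) | Selective, ρ = 0.3 | Selection cost, ρ = 0.3 (points) |
|---|---|---|---|---|---|
| −3 | 79.8% | 77.7% | 2.1 | 78.5% | 1.3 |
| −2 | 79.1% | 75.8% | 3.3 | 77.0% | 2.1 |
| 0 | 76.1% | 69.3% | 6.8 | 72.3% | 3.8 |

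Over SD 2, 3, 4, c = −3, −2, −1, 0 and ρ = 0.3, 0.6, the difference runs from 1.385 to 1.970 and the selection cost from 0.1 to 6.9 points. In this model the expected order of the levels is not reversed.

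**6. Loss through missed sessions.** If 2 of 15 patients are lost from one level and average 1 SD (3 points) below its mean, the mean of the other 13 rises by 3 × 2/13 = 0.46. The difference of 2.0 becomes 2.46 if they came from the better level and 1.54 if from the worse.

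**The case against.** The strongest reply is that the harm depends on one reading of a loosely drafted list. The list sits under Interventions, where a rule for stopping treatment belongs. The Outcomes section schedules clinical measures three times without naming an exception. Worsening is a sensible safety reason to stop stimulation in stroke patients, and seizures are among the adverse events to be recorded. All of this stands: the text is ambiguous and is not an explicit order to remove patients.

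A reader might infer more than the article supports:

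- That a patient who stops early can never reach W5. W5 and W17 are also week labels, and a patient who stops in week 2 can attend both. The tie to 20 sessions only makes the visit unclear for such a patient.
- That loss according to response is certain. Worsening is undefined and is not tied to MoCA. If it means only treatment-related symptoms, the loss follows tolerability.
- That the calculations measure the bias. Every input is assumed, and the removal variable was given the same level means as MoCA change, so better levels lose fewer patients by construction. If intolerance rose with intensity or pulse number regardless of benefit, the pattern would differ. The heaviest case, about 26% lost overall, has no support in the document.

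It may also be said that follow-up after stopping treatment, and the analysis set, are details for the full protocol or the analysis plan. That is fair for missing-data methods, and no complaint is made of their absence. It does not dispose of a criterion that is printed here, governs conduct and can be followed as study exit.

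**Conclusion.** The point holds as a conditional one. The list does not separate stopping rTMS from leaving the study, study exit is at least as natural a reading, and no statement keeps these patients in follow-up. If applied that way, outcomes are lost in relation to tolerability and, where worsening covers clinical or cognitive decline, to response. Loss that tracks response tends to shrink the differences between levels, while loss through missed sessions can push a difference either way.

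The size cannot be derived from the article. On the assumed inputs it runs from negligible to moderate, and the zero-loss benchmark is one that better follow-up would approach but not guarantee. This is a worthwhile, inexpensive improvement and not proof that the trial's results will be biased. Confidence is medium because the sponsor may already intend a treatment stop only.

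**What to change.** State under Discontinuing criteria that failure to complete the course and worsening symptoms end rTMS only. Assess every randomised patient who has not withdrawn consent at W5 and W17, with both visits timed from the start of treatment and not from completion of 20 sessions, and keep each patient in the allocated group. It would also help to define worsening as a safety stopping rule and to move the missing-baseline item to eligibility before randomisation.

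The cost is a few lines of text and a few extra follow-up contacts at visits already scheduled. The article reports that recruitment was under way, so patients entered after the change would benefit. The downside is slight dilution of the level differences by patients who stopped early. Patients who withdraw consent or become untestable will still be lost. If the sponsor already intends a treatment stop only, the change just makes that explicit.

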### 3. Outcomes

The primary outcomes are the Montreal Cognitive Assessment Beijing Version (MoCA-BJ) and the Trail-Making Test (TMT). The secondary outcomes are the modified Barthel index (MBI), the Lawton Instrumental Activities of Daily Living Scale (LIADL), the stroke-specific quality of life (SS-QOL), the functional magnetic resonance imaging (fMRI) scan and the adverse events. All measurements of clinical assessments were administered three times: pre-treatment (baseline), post-treatment, and at a three-month follow-up. All of the cognitive assessments were performed by a trained neuropsychologist who was blind to the treatment status of the participants throughout the study. The MRI scan were conducted at baseline and at the end of rTMS treatment.

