#### (2) TMT

The trail marking test (TMT) was firstly used in 1944 for America army individual intelligence assessment [22]. Nowadays, it is widely employed as a diagnostic tool for visual attention and executive functioning and the processing speed for neuropsychological diseases [23, 24]. It consists of two parts in which the subject is instructed to connect a set of 25 circles containing numbers (Part A) or numbers and letters (Part B) arrayed pseudorandomly on a letter-size sheet of paper as fast as possible while still maintaining accuracy.

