### 4. Statistical analyses

The data of MoCA-BJ, TMT, MBI, LIADL and SS-QOL were shown as mean ± standard deviation (SD) and analyzed by the range analysis and one-way analysis of variance (ANOVA), which was used the SPSS 22.0 software (IBM, Armonk, NY, USA, 2020). The range analysis was used to determine the influence of each parameter at a specific level on the effect indicator and obtain the optimum combination of rTMS parameters. The one-way ANOVA was used to determine the statistical significance in nine different parameters’ combination of rTMS. P < 0.05 was considered significant.

For ALFF and FC maps, paired T-test will be used for intra-group comparison and one-way ANOVA analysis will be used for inter-group comparison in the three stimulating site subgroups. Then multiple comparison correction will be performed using Gaussian random field theory (GRF) with voxel *p* < 0.005, cluster *p* < 0.05. The Pearson correlation analyses were used to calculate the correlations between the changes in ALFF and FC with the clinical symptom scores at baseline and the end of the rTMS treatment (*p* < 0.05).

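### Two unranked primary outcomes at two visits share an unsplit 0.05, and each score's range analysis names its own optimum, though the trial seeks one regimen

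*Protocol article*

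**What the plan says.** Section 3 (Outcomes) of the protocol article names two primary outcomes: "The primary outcomes are the Montreal Cognitive Assessment Beijing Version (MoCA-BJ) and the Trail-Making Test (TMT"). It does not order them, and it does not say whether success needs both or either.

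On the TMT, section 3(2) says: "It consists of two parts in which the subject is instructed to connect a set of 25 circles", one part with numbers and one with numbers and letters. It does not say which part, or which combination of the two, is the primary score.

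On timing, section 3 says: "All measurements of clinical assessments were administered three times: pre-treatment (baseline), post-treatment, and at a three-month follow-up". The participant timeline places the post-baseline assessments at "termination of 20 rTMS sessions (W5) and the follow-up (W17"). Neither visit is called primary.

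On analysis, section 4 says: "The data of MoCA-BJ, TMT, MBI, LIADL and SS-QOL were shown as mean ± standard deviation (SD) and analyzed by the range analysis" and by one-way ANOVA. The two tools have different jobs. Range analysis gauges each parameter's influence on an outcome and yields the optimum combination. For the other: "The one-way ANOVA was used to determine the statistical significance in nine different parameters’ combination of rTMS". The threshold for these clinical scales is: "P < 0.05 was considered significant". The same section specifies a multiple-comparison correction (Gaussian random field) for the ALFF and FC maps only.

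**The concern.** The trial aims to identify an optimum parameter regimen, in the singular. The stated plan does not lead to one. Each primary outcome has its own significance test at the full 0.05 and its own optimum, and no rule says which one speaks for the trial.

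These are two distinct defects. The error rate belongs to the ANOVA, because several primary tests at 0.05 give more than a 5% chance that at least one is falsely positive. The conflicting optima belong to the range analysis. It has no significance level and always returns a best combination, whether or not the differences are real. If MoCA-BJ and TMT, or week 5 and week 17, favour different settings, nothing in the plan decides between them, and the choice could be made with the results in view.

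**Working it through.** **Inputs from the article.** There are 45 patients, 9 groups × 5 = 45 (section 1(4)). Each of the four factors has three levels, so each level mean rests on 45 / 3 = 15 patients. The ANOVA therefore has 9 − 1 = 8 and 45 − 9 = 36 degrees of freedom, with a 5% critical value of 2.209. There are two named primary outcomes and two post-treatment visits. The threshold is 0.05.

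**The plan's own figure.** One test at 0.05 gives 1 − 0.95 = 0.05, so the stated threshold is a per-test level. The sample size rests on funding, feasibility and a neuroimaging median. No power calculation is given, so there is none to reproduce.

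**Number of primary tests, by reading.**
- Two: MoCA-BJ and one TMT score, at one visit.
- Three: MoCA-BJ, TMT-A and TMT-B, at one visit.
- Four: MoCA-BJ and one TMT score, at two visits.
- Six: three scores at two visits.

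**False-positive chance if the tests are independent**, 1 − 0.95^k:
- k = 2: 9.75%
- k = 3: 14.3%
- k = 4: 18.5%
- k = 6: 26.5%

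**With correlated scores.** The article gives no correlations, so a common correlation from 0 to 0.9 is assumed. The design in Table 2 was simulated with normal data, 5 patients per group and 20,000 runs per setting:

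| Assumed correlation | 2 tests | 6 tests |
|---|---|---|
| 0 (formula) | 9.75% | 26.5% |
| 0.3 | 9.8% | 25.5% |
| 0.5 | 9.2% | 22.4% |
| 0.7 | 8.7% | 18.4% |
| 0.9 | 7.5% | 12.0% |

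The 9.8% against 9.75% is simulation error. Every entry exceeds 5%.

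**Do the optima agree?** Range analysis was represented as choosing the best level mean for each factor, which gives one of 3^4 = 81 combinations. With no effects and independent scores, two scores match with probability (1/3)^4 = 1/81 = 1.2%. Two scenarios were simulated: no effect of any factor, and an assumed 0.5 SD advantage for one level of every factor, identical on every score. The table shows how often all the optima coincide:

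| Assumed correlation | 2 scores, no effect | 2 scores, 0.5 SD | 6 score-visits, no effect | 6 score-visits, 0.5 SD |
|---|---|---|---|---|
| 0 | 1.2% | 31% | about 0% | 2% |
| 0.3 | 4% | 36% | about 0% | 6% |
| 0.5 | 8% | 41% | under 0.1% | 11% |
| 0.7 | 17% | 50% | 0.7% | 19% |
| 0.9 | 39% | 68% | 10% | 40% |

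So even when one true optimum exists and is shared by both outcomes, two scores disagree in about 32–69% of trials.

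The group list printed below Table 2 differs from the table for several groups. The simulation uses Table 2. The ANOVA error rates do not depend on which version is right.

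**The case against.** The strongest reply is that an article may leave the primary TMT score, the primary visit and the multiplicity method to an analysis plan that is not shown. That stands as far as silence goes, and such a plan may hold a rule. But the point rests on what the article states: two primaries of equal rank, one threshold for all the clinical scales and an optimum taken from each scale. It also addresses multiplicity in the same section, and only for the imaging maps. Followed as written, these choices do not yield one regimen.

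A second reply is that the aim is exploratory and no power is claimed. That softens the weight of the error rate, but not the need to say which result names the optimum.

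Several stronger readings are tempting, and the documents do not support them:
- *Six primary tests are planned, with 26% error.* Describing the TMT's two parts does not make each a primary score, and listing visits does not prescribe an ANOVA at each. Six is the upper reading, and 26.5% also needs independence.
- *The inflated error is the chance of recommending a wrong regimen.* It is not. The nine-group F test selects no optimum, and the range analysis that does so has no error level.
- *The optima will agree only 1 time in 81.* That holds only for independent scores with no effects. Scores from the same patients will probably correlate, and agreement then rises as shown.
- *The plan points to MoCA-BJ at week 5 as the proper endpoint.* Nothing in the article ranks it above TMT or above week 17.

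If significance on both outcomes were required, the false-positive rate would not be inflated. The article states no such rule.

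**Conclusion.** The concern holds in two separate parts.

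1. With each primary ANOVA tested at 0.05, the chance of at least one false positive is about 7.5–10% for two tests and about 12–26% for six. The six-test count is an assumption about how TMT and the visits are handled. Both ranges rest on assumed common correlations of 0 to 0.9 and normal data.
2. The per-score optima will often conflict. Two scores agree about 31–68% of the time under the assumed 0.5 SD advantage shared by every score, and 1–39% of the time with no effects. As nothing decides between them, the reported regimen could be picked after the data are seen.

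The second part matters more, because it bears directly on the trial's stated aim, and splitting alpha would not cure it. The sponsor should act, but the flaw lies in wording and does not undermine the design.

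**What to change.** Before unblinding, name one score at one visit (for example MoCA-BJ at W5) as the single primary endpoint. That endpoint is tested at 0.05, and its range analysis alone determines the optimum. Report the other scores now called primary, and the other visit, as secondary: either Holm-adjusted or labelled exploratory. State whether they agree with the chosen optimum, without letting them replace it. Specify which TMT score is meant in either case.

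If both primaries are kept, apply Holm across them. With two tests, the smaller p-value is compared with 0.05 / 2 = 0.025 and, if that is met, the larger with 0.05. In addition, prespecify a composite or a joint rule that yields one optimum, since Holm by itself does not.

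The cost is a change to the outcome and analysis wording and an update of the registry entry, with no extra patients or visits. The score that is not chosen, TMT in the example, loses its primary status. The change gives one answer, not a precise one: under the same 0.5 SD scenario, a single score identified all four best levels in only about 53% of simulated trials, and the report should say that the optimum is uncertain.
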